### 13.2 Data entry and modification

The data managers of the statistical institution are responsible for data entry and management using excel or EpiData2.1 database. The data are required to be double entered by two independent data managers and verified to ensure data accuracy.

The data manager will fill out the DRQ in response to any doubts in the CRF and send queries to the investigators through clinical monitors; the investigators should answer the questions promptly and respond back. The data manager will modify the data per the investigator's response, verify and enter the modifications, and re-issue the DRQ if necessary.

### 13.3 Blind review and database lock

The principal investigator, sponsor and statistical analyst will lock the database after completing the blind review and confirming correctness of the constructed database.

### 13.4 Unblinding

Once all the study data have been reviewed and locked, the principal investigator (PI), statisticians and sponsor will jointly discuss the statistical plan, unblind this study and co-sign the blind codes.

Any modifications of the database after unblinding must be approved by the principal investigator, biostatisticians and data manager in written prior to implementation.

Once received the blind codes, the statistical analysts will carry out statistical analysis per the statistical plan and eventually write the statistical analysis report based on which the principal investigator will write the clinical trial summary report.

## 14. Statistical analysis

See the “statistical analysis plan” for details of statistical analysis. Before database lock, the statisticians, principal investigator and sponsor will jointly discuss and finalize the statistical plan in accordance with the data characteristics. This protocol only provides the general statistical requirements.

### 14.1 Primary Populations

The primary efficacy variable will be summarized and analyzed in ITT and PP populations, the secondary efficacy variables will be summarized and analyzed in ITT populations. ITT population will be the primary analysis population.

✧ Full analysis set (FAS): refers to the set of eligible cases and dropout cases excluding the

rejected cases. The ITT population will be defined as all randomised patients having received at least one dose of either the tested or the reference treatments.

- ✧ Per protocol set (PPS): The PP population will be defined as all the subjects who completed the treatment period without any major deviation from the protocol.
- ✧ Safety set (SS): Safety population will be defined as all the subjects who received at least one treatment and have actual data of safety indexes.

## 14.2 Statistical Analysis Method

### 14.2.1 Demographic Characteristics

(1) Consistency with normal distribution: Because this is a randomized and blinded trial with a large sample size, the data is acceptable when close to normal distribution. Appropriate statistical methods or data transformation will be adopted for non-normal distributed data, D method, W method or moment method will be used.

(2) Presence of outliers: statistical and clinical analysis should be carried out to determine the acceptance and rejection.

(3) Handling of the missing values of primary efficacy index: if the primary efficacy data of an individual subjects is missing, missing data were imputed as non-responses.

(4) Analysis of the subjects who did not complete this trial: the cause of each dropout case should be analyzed.

(5) Descriptive statistics: provide the mean, standard deviation, maximum, minimum, median, confidence interval, frequency (constituent ratio), etc.

### 14.2.2 Statistical inference method

(1) Measurement data: t-test, paired t-test, rank sum test, paired rank sum test, median test method, etc.

(2) Numeration data: chi-square test, Fisher's exact test, etc.; Redit analysis and CMH method can be used to test the ranked data.

(3) Primary efficacy: The response rate will be analyzed using Cochran–Mantel–Haenszel test. Logistic regression analysis, with center and PWS type as covariates will be used to compare treatment group versus placebo group on primary efficacy. If baseline variables are not balanced between groups, non-balanced variable will be also included as covariates in the model. For response rate at week 8, missing data were imputed as non-responses.

(4) Difference analysis: in primary efficacy analysis, a 40% difference between the treatment and placebo group in response rate is expected to be detected.

### 14.2.3 Statistical presentation

- (1) The report mainly uses the self-evident tables that include title, notes and number of cases.
- (2) The results of repetitively measured data use both tables and the annexed statistical charts at the same time to improve readability.
- (3) Difference analysis is represented by the two-sided 95% confidence interval for the intergroup difference in efficacy; all the general statistical tests are two-sided tests,  $P \leq 0.05$  is considered to have statistical significance.

#### 14.3 Statistical software

All statistical analyses will be carried out by the SAS statistical software package (version 9.1.3).

#### 14.4 Interim analysis

This study does not have interim analysis. If special circumstances including uncertain efficacy or safety issues emerge during this trial, the sponsor, investigators and statisticians will jointly discuss the issues and make decisions.

#### 14.5 Contents of statistical analysis

1. Case distribution: provide the sizes of different data sets of all groups, distribution of the cases among all centers, comparison of the total dropout rate, and a detailed listing of the reasons for termination.
2. Comparability analysis: demographic data and other baseline indexes are compared to measure the intergroup comparability.
3. Compliance analysis: (1) Drug compliance analysis: compare whether the patients of the two groups have taken the correct doses of trial drugs in timely manner without using the prohibited drugs and food as described in this protocol. (2) Drug combination analysis: count the number of subjects receiving drug combination in each group and provide a detailed list.
4. Efficacy analysis: PP and ITT analysis of the primary efficacy should be carried out at the same time; because this study is a multicenter clinical trial, the impact of center effect on the efficacy should be considered during analysis.
5. Analysis of the efficacy influencing factors: if there are significant differences in age, gender, disease types, disease conditions and other factors between the two groups before drug treatment or relevant factors significantly affecting the efficacy (e.g. drug combination) during the trial process, these factors should be used as covariates for analysis of covariance or logistic regression analysis during intergroup efficacy comparison.
6. Safety analysis: based on the requirements for correlation of adverse reactions, use listings to describe the AEs and adverse reactions in both groups (including the number of cases of various

AEs, the number of cases with "normal shift to abnormal" or "exacerbation of the abnormality" of the laboratory test indexes and abnormal conversion rate before and after this trial), list the causes and explain. Chi-square test is used for statistical analysis of the adverse reactions.

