## 3. Trial design

### 3.1 Design principle:

This is a parallel, placebo-controlled, double-blinded and multicenter clinical trial.

The subjects are randomized into trial group and control group at 3:1 ratio in this phase III clinical trial.

Statistical estimation of the sample size: using two-sided test of the efficacy,  $\alpha=0.05$  and  $\beta=0.1$  (power=90%) based on phase II clinical trial results, the expert panel estimates the total clinical efficacy rate of hemoporphin for injection to be 75.0% in the treatment of port-wine stains and expects a 40% difference from the placebo group; consequently, the estimated minimal number of subjects is 66 for the trial group and 22 for the control group.

In compliance with the SFDA requirement of minimum sample size of no less than 300 subjects for phase III clinical trial group, and also taking into account of dropout, the sample size of this clinical trial was determined to be 330 subjects for the trial group and 110 subjects for the control group, giving a total of 440 subjects.

The subjects will be assigned into trial group or control group by stratified block randomization to receive not more than 2 courses of treatment. The control group receive placebo during the first course of treatment followed by trial drug during the second course of treatment. Each course of treatment will last for 8 weeks. Based on the phase II clinical trial results, the trial drug dose is set at 5mg/kg.

The trial design profile is shown in the following table.

| Trial period                   | Hemoporphin for injection dose | Group and number of cases     | Design principle                                                          |
|--------------------------------|--------------------------------|-------------------------------|---------------------------------------------------------------------------|
| The first course of treatment  | 5mg/kg                         | 330 subjects in trial group   | Randomized, double-blinded, placebo and parallel-controlled (multicenter) |
|                                | 0mg/kg                         | 110 subjects in control group |                                                                           |
| The Second course of treatment | 5mg/kg                         | 330 subjects in trial group   | Randomized, double-blinded (multicenter)                                  |

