- 5) Precautions: the patients should be instructed to observe the photoreaction after drug infusion and pay attention to photo protection. The photoreaction is expected to disappear completely in approximately 10 days after drug infusion. During the light protection period (2 weeks), the subjects should pay attention to protection of the exposed skin and eyes, avoid irradiation of sunlight or strong indoor lights. In case of drug extravasation during the infusion, the extravasation area must be kept completely away from light for a fairly long time until local swelling and discoloration disappears completely, otherwise severe local skin photoinjury may occur.
- 6) PDT may cause the following treatment reactions: the patients may experience itching, burning sensation, pain, swelling, blisters and scabs at the irradiated and surrounding area. These therapeutic responses are usually transient and self-healing without special treatment.
- 7) Adverse reactions: If light protection measures are not taken properly, some patients may experience photosensitive reactions such as photosensitive dermatitis, photosensitive ophthalmia, photosensitive cheilitis, etc; some patients may experience nausea, dizziness, headache, drowsiness, total bilirubin elevation, hyperpigmentation, hypopigmentation,

treatment site infection, scarring and other adverse reactions.

- 8) At week 8 after the first treatment, if the color of treatment area has not subsided completely and there are no serious pigmentation, scarring and other conditions that are unsuitable for re-treatment according to the investigator's judgment, the next stage treatment can be carried out.

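### Section 14.5 item 5 allows factors arising after randomisation into the between-group efficacy comparison, and sections 14.2.2 and 14.5 pick further baseline covariates by observed imbalance

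*Protocol*

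**What the plan says.** Two rules in the protocol decide which covariates enter the efficacy model.

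- **Section 14.2.2, item (3), primary efficacy.** It names a test ("The response rate will be analyzed using Cochran–Mantel–Haenszel test") and a model: "Logistic regression analysis, with center and PWS type as covariates will be used to compare treatment group versus placebo group on primary efficacy". It then adds: "If baseline variables are not balanced between groups, non-balanced variable will be also included as covariates in the model". It gives no threshold for imbalance and no list of candidate variables.
- **Section 14.5, item 5, factors influencing efficacy.** Its first trigger is baseline imbalance: "if there are significant differences in age, gender, disease types, disease conditions and other factors between the two groups before drug treatment". Its second trigger concerns events after treatment has begun: "relevant factors significantly affecting the efficacy (e.g. drug combination) during the trial process, these factors should be used as covariates". Either way the factor enters an analysis of covariance or logistic regression for the comparison between groups.

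Section 14 has the statisticians, principal investigator and sponsor "jointly discuss and finalize the statistical plan in accordance with the data characteristics", before database lock. Section 14.2.3 item (3) requires a two-sided 95% confidence interval for the difference in efficacy between groups.

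**The concern.** Randomisation makes the groups comparable on everything fixed before treatment. It gives no such protection for what happens afterwards. If treatment changes how many subjects take a concomitant drug, users in the active group and users in the placebo group are different kinds of subject. Comparing groups within levels of use then mixes the treatment effect with that difference. If the drug itself alters the response, adjustment instead removes part of the effect under study.

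A link between treatment and concomitant use is possible here. Section 4.3 item 6 warns that "the patients may experience itching, burning sensation, pain, swelling, blisters and scabs at the irradiated and surrounding area", and such reactions could lead to drug use. The clause also selects the covariate for its observed association with efficacy, so the outcome data help to choose the model.

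The baseline rule is a different and milder problem. Imbalance between groups can be seen only once the codes are open. Finalising the plan under blind therefore cannot settle the covariates while this rule stands.

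**Working it through.** **1. The plan's own figure.** Section 3.1 gives a "using two-sided test of the efficacy", alpha 0.05, power 90%, response 75% on active, a 40-point difference (so 35% on placebo) and 3:1 allocation, and arrives at 66 + 22. Full enumeration of the two-sided Fisher exact test gives power 88.5% at 63/21 and 90.3% at 66/22, so the figure reproduces. At the planned 330/110, power (normal approximation) is above 99.9%. Nothing below changes either size.

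**2. Post-randomisation covariate, no true treatment effect.** Assumed model for 330 active (T = 1) and 110 placebo (T = 0) subjects, 2,000 runs per cell:

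- U is an unmeasured prognosis, standard normal.
- Concomitant use M: logit P(M = 1) = −1.5 + a·T − g·U.
- Response Y: logit P(Y = 1) = −0.7 + 1.0·U, with no treatment term.
- Rule: M enters the logistic model if its Wald |z| exceeds 1.96.

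At U = 0, use is 1/(1 + e^1.5) = 18% on placebo. On active it is 18%, 32%, 50% and 73% for a = 0, 0.75, 1.5 and 2.5.

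| a (treatment on use) | Type I error under the rule, g = 0.5 / 1.0 / 1.5 | Bias in risk difference, points |
|---|---|---|
| 0 | 4.6% / 4.4% / 5.4% | −0.2 / −0.2 / −0.1 |
| 0.75 | 6.4% / 5.7% / 7.2% | +0.9 / +1.9 / +2.5 |
| 1.5 | 8.3% / 10.7% / 15.4% | +1.9 / +4.0 / +5.0 |
| 2.5 | 12.0% / 25.4% / 34.1% | +2.9 / +7.0 / +8.3 |

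Without M the error was about 4% to 5.4% throughout. The simulation standard error at 5% is √(0.05 × 0.95 / 2,000) = 0.5 points, so the lowest non-zero-link result (5.7%) is close to nominal. The bias is positive because poorer prognosis was assumed to raise use; reversing the sign of g reverses it.

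**3. Post-randomisation covariate, true effect near 40 points.** In an assumed shared-prognosis scenario, the estimate moved from 40.5 points unadjusted to 44.3 under the rule. In an assumed mediator scenario, it fell from 38.7 to 26.5. The null hypothesis was rejected in at least 99.9% of runs in both.

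**4. Baseline imbalance rule.** With k independent baseline variables each tested at 5%, the chance that at least one enters by chance is 1 − 0.95^k:

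- k = 3: 14.3%
- k = 4: 18.5%
- k = 6: 26.5%
- k = 10: 40.1%

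These are rates of model change, not error rates. Simulated type I error under the rule (3,000 runs per setting, four or six prognostic variables) was 3.7% to 4.8%. For a moderate effect (treatment log-odds ratio 0.6; four covariates, each with log-odds ratio 0.5 per standard deviation), power was:

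- 57.6% unadjusted
- 58.5% under the imbalance rule
- 66.8% with the same four covariates fixed in advance

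The mean estimated log-odds ratio was 0.502 under the rule and 0.605 with fixed covariates. The odds ratio being estimated therefore also depends on which covariates enter.

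**5. The two sections side by side.**

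| | 14.2.2 item (3) | 14.5 item 5 |
|---|---|---|
| Always included | Centre, PWS type | None named |
| Baseline trigger | Not balanced, undefined | Significant difference |
| Candidates | Any baseline variable | Four named kinds, then open |
| Post-randomisation factors | Not mentioned | Included |

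**The case against.** **Item 5 is not labelled primary.** It stands apart from the primary efficacy item in section 14.5, and section 14.2.2 item (3) mentions baseline variables only. Neither rule alters the CMH test. This stands: the post-randomisation clause may have been meant as supportive. But it is an instruction for the comparison between groups and is not labelled exploratory, and the imbalance rule does sit in the primary efficacy paragraph.

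**The link from treatment to concomitant drugs is not shown.** Section 4.3 says the reactions usually pass without special treatment. Section 4.8 speaks of concomitant drugs for other diseases and bars those in the exclusion criteria. This also stands. A reader might infer that local reactions, and so drug use, occur mainly on active treatment; no section says so. The bias is therefore possible, not established.

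**Every simulated strength is assumed.** That is correct. The top of the range needs use of about 18% against 73% together with a strong shared cause.

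**The imbalance rule does not inflate type I error.** This is right, and that rule should not be charged with bias. Section 14.5 names age, gender, disease types and disease conditions. If disease type means PWS type, it is already fixed, and three named factors remain (14.3%), though the list is left open.

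**Conclusion.** The point holds as a should-fix. Followed as written, the post-randomisation clause can bias the effect estimate in either direction and can inflate type I error, but only if treatment influences the factor adjusted for. The simulated range of about 6% to 34% rests on strengths the protocol does not supply; without that influence there is no inflation.

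A reader might infer that the trial's significance conclusion is in danger. At 330/110 with the planned 40-point difference it is not, in the scenarios examined. What is exposed is the size of the effect and the confidence interval that section 14.2.3 requires.

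A reader might also infer that the primary model has no fixed covariates. It has two, centre and PWS type; only the further ones depend on imbalance. The cost of that rule is a model known only after unblinding and lower precision than fixed prognostic covariates would give (58.5% against 66.8% power in the assumed case).

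An unseen statistical analysis plan does not remove the point, since the protocol itself states both rules.

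**What to change.** 1. In section 14.5 item 5, delete the clause on factors arising during the trial from the efficacy comparison. Report concomitant drugs descriptively by group, or use them only in an analysis labelled exploratory.
2. In sections 14.2.2 item (3) and 14.5 item 5, replace the imbalance trigger with a closed list of baseline covariates named before unblinding: centre, PWS type and, if wanted, for example age and sex.
3. Make both sections state the same rule.

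No change of test is needed for this point. Whether the CMH test or the logistic model is decisive is a separate question.

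The cost is protocol wording only. Sample size, data collection and conduct are unaffected.

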## 2. Trial purpose

This study is to evaluate the efficacy and safety of hemoporphin for injection for the treatment of port-wine stains using placebo as the control in two stages of PDT treatments. Primary endpoint will be established at the first stage, and safety analysis will include both stages.

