#### 6. Trial arrangement

- Treatments: up to 2 times (the patients can receive an additional treatment if the treatment area did not subside completely after the first treatment)
- Efficacy evaluation: the efficacy evaluation is carried out in Week 8 after each treatment; both

evaluations are compared to the disease conditions before the treatment.

- Laboratory examination: the testing is carried out before each treatment and on Day 4 after the treatment.

Trial Flowchart

|                                   | PDT treatment                 |       |                                |       | Efficacy observation                                        |
|-----------------------------------|-------------------------------|-------|--------------------------------|-------|-------------------------------------------------------------|
|                                   | The first course of treatment |       | The Second course of treatment |       | The first/second course of treatment
Week 8 of treatment |
|                                   | Day 1                         | Day 4 | Day 1                          | Day 4 |                                                             |
| Instructions for patients         | ×                             |       |                                |       |                                                             |
| Signing ICF                       | ×                             |       |                                |       |                                                             |
| Laboratory examination            | ×                             | ×     | ×                              | ×     |                                                             |
| Inclusion criteria                | ×                             |       |                                |       |                                                             |
| Exclusion criteria                | ×                             |       |                                |       |                                                             |
| History                           | ×                             |       |                                |       |                                                             |
| Accompanied diseases              | ×                             |       |                                |       |                                                             |

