## 9. Safety

9.1 The adverse events (AE) are identified through inquiries of the subjects (caution: avoid inductive questioning, phrases such as "how do you feel after the treatment?" can be used during the inquiry), physical examination and comparisons of the laboratory examination results before and after the treatment including blood routine, urine routine, liver function, kidney function, ECG recording.

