### 9.2 Adverse events

9.2.1 Definition: "AE" is any adverse medical events occurred after the subjects have received the drug, which may be unrelated to the treatment. Accordingly, AE can be any discomforts and unaware signs (e.g. abnormal laboratory examination results), symptoms or diseases.

- ☞ All AEs must be recorded in CRF regardless of their severity and relationship with the used drug. For all the subjects who withdraw from this study due to AEs, the investigators should continue to follow-up with them until full recovery, record the relevant data, and indicate AE occurrence date and recovery date in the CRF.

9.2.2 Correlation assessment: the investigators should evaluate the correlation of the AEs with drug treatment in this trial as follows:

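### Section 14.5 item 6 sets the laboratory conversion rate at trial level, although testing and comparison run per treatment; the shift summary can miss a transient first-course abnormality and blur the placebo contrast

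*Protocol*

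**What the plan says.** Section 14.5 item 6 lists the safety outputs. It says to "use listings to describe the AEs and adverse reactions in both groups". Inside the same item it asks for the number of subjects whose results move from normal to abnormal or worsen from an abnormal start, and for the "laboratory test indexes and abnormal conversion rate before and after this trial". It names no visits.

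Elsewhere the protocol works by treatment:

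- Section 6: "the testing is carried out before each treatment and on Day 4 after the treatment". A subject treated twice therefore has four planned tests.
- Section 9.1: adverse events are identified partly through "comparisons of the laboratory examination results before and after the treatment including blood routine, urine routine, liver function, kidney function, ECG recording".
- Section 9.2.1: "AE can be any discomforts and unaware signs (e.g. abnormal laboratory examination results), symptoms or diseases", and "All AEs must be recorded in CRF regardless of their severity and relationship with the used drug".
- Section 2: "safety analysis will include both stages".

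Section 3.1 gives the control group placebo in the first course and active drug in the second. Section 4.3 item 8 makes the second course conditional on incomplete clearance at week 8 and on suitability for re-treatment.

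**The concern.** The Day 4 tests are the only scheduled laboratory look after each infusion, and the protocol expects at least one laboratory reaction: section 4.3 item 7 says that "some patients may experience nausea, dizziness, headache, drowsiness, total bilirubin elevation, hyperpigmentation, hypopigmentation" may occur. If the laboratory summary compares the state before the trial with the state after it, the natural pair in a re-treated subject is the first pre-treatment test and the Day 4 test of the second course. The two tests in between then play no part.

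Two things are at stake. First, an elevation that follows the first infusion and resolves by week 8 would be scored as no change in a re-treated subject, but as a shift in a subject who stops after one course. Scoring would then depend on whether the lesion cleared and on suitability for re-treatment. Second, the last test in a re-treated control follows an active infusion. The contrast that randomisation protects, drug against placebo in the first course, is then not what the table shows.

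**Working it through.** The protocol states no figure that could be reproduced, so the check is first a comparison of the sections and then an illustration.

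**1. Sections side by side.** Section 6 gives four tests in a re-treated subject: before treatment and Day 4 in each of two courses. Section 9.1 compares around the treatment. Section 14.5 item 6 compares around the trial. For a subject with one course the two units coincide. For a subject with two courses they do not.

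**2. Hypothetical bilirubin records.** These are constructed to show the scoring and are not taken from the protocol.

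| Record | Course 1 pre | Course 1 Day 4 | Course 2 pre | Course 2 Day 4 | Pre-trial vs last test | Per course, any shift |
|---|---|---|---|---|---|---|
| A | normal | high | normal | normal | no shift | shift |
| B | normal | normal | normal | high | shift | shift |
| C | normal | high | not given | not given | shift | shift |

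A and C have the same first-course finding but score differently under the trial-level reading.

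**3. Possible undercount in the trial group, if that reading is applied.** Inputs: 330 subjects (section 3.1). Assumed, because the protocol gives neither: probability p of a transient Day 4 abnormality per active infusion, and share r re-treated. Also assumed: courses independent, and recovery by week 8.

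- Rate with a shift after any treatment = p + r·p·(1 − p)
- Rate from pre-trial vs last test = p
- Subjects absent from the shift table = 330·r·p·(1 − p)

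At p = 10%, r = 70%:

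- Any treatment: 0.10 + 0.70 × 0.10 × 0.90 = 16.3%
- Pre-trial vs last test: 10.0%
- Absent: 330 × 0.70 × 0.10 × 0.90 = 20.8, about 21 subjects

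Other values for the number absent:

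| p | r = 50% | r = 80% | r = 100% |
|---|---|---|---|
| 1% | 1.6 | 2.6 | 3.3 |
| 5% | 7.8 | 12.5 | 15.7 |
| 10% | 14.8 | 23.8 | 29.7 |

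The count runs from under 2 to about 30 according to the assumptions, so none of these values is an estimate for this trial.

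**4. Placebo contrast.** Take p = 10% and r = 70% in both groups, and assume no background abnormality on placebo.

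- First course, Day 1 to Day 4: 10% vs 0%, a difference of 10 points.
- Pre-trial vs last test: trial group 10%; control group r·p = 0.70 × 0.10 = 7%; difference 3 points. If every control were re-treated, the control rate would be 10% and the difference 0.
- Pre-trial vs any later test: 16.3% vs 7%, difference 9.3 points, but this sets up to two active infusions against at most one.

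Under neither trial-level reading is the result a drug-against-placebo comparison. Only the first-course Day 1 to Day 4 change is.

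**The case against.** The strongest reply is that the protocol writes no first-versus-last rule. Item 6 names no visits and does not exclude the Day 4 test of the first course. In a translated text the phrase can equally mean normal at baseline and abnormal at any later test, and it may qualify only the conversion rate and not the two shift counts. Section 9.1 describes how events are detected and item 6 lists report contents, so they need not clash. Section 14 leaves details to a statistical analysis plan, which is not among the documents and may define the time points.

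A reader might also infer that first-course abnormalities go uncounted altogether in re-treated subjects. The documents do not support that. Under 9.1 and 9.2.1 an abnormal result after either treatment can be an adverse event and must be recorded, and item 6 itself requires counts of adverse events. Nor do they support presenting any percentage of missed cases as a property of the plan, since the abnormality and re-treatment rates are both absent.

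Most of this stands. It reduces the undercount to a possible consequence of one plausible reading, confined to the shift counts and conversion rate. It does not remove the mismatch in unit: the protocol chose the trial as the unit in item 6 and the treatment in sections 6 and 9.1. It also leaves the placebo point untouched, because controls cross to active drug on either trial-level reading. And if the conversion rate disagreed with the adverse event counts in the same report, that would itself need explaining.

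**Conclusion.** The wording of section 14.5 item 6 does not match sections 6 and 9.1 and should be reconciled with them. On the plain reading of pre-trial against last test, a transient abnormality after the first infusion can drop out of the laboratory shift summary in re-treated subjects, while remaining recordable and countable as an adverse event. The figure of about 21 of 330 is illustrative only. It needs that reading, p = 10%, r = 70%, independent courses and recovery by week 8, and it vanishes if any later abnormality counts.

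The blurring of the placebo contrast is the firmer part. It follows from controls receiving active drug in the second course and does not depend on which trial-level reading is used, though its size again rests on rates that the protocol does not state. This is a correctable weakness in one safety summary. It does not show that the trial fails to capture laboratory harm.

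**What to change.** Replace the trial-level phrase in section 14.5 item 6 with a per-course derivation that agrees with sections 6 and 9.1:

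- Compare each course's Day 4 result with that course's own pre-treatment result.
- Count a subject as shifted or worsened if this happens after any treatment.
- Tabulate first-course Day 1 to Day 4 by randomised group, and label it as the placebo-controlled laboratory comparison.

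The cost is an amended sentence and one extra table. All the values are already scheduled for collection, so no visit or test is added. The downside is that the reported abnormality rate may look less favourable than under a pre-trial against last-test comparison.
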